### Study design and setting

A multiple baseline study [50] will be conducted involving all 56 community health facilities in a single health service in New South Wales, Australia. The service provides comprehensive healthcare to approximately 840000 people residing in metropolitan, regional, rural and remote location, and employs over 1400 community health clinicians who see in total approximately 57000 clients per year.

The study will involve the sequential implementation of a 12 month practice change intervention in three administratively defined groups of community health facilities (Figure 1). The intervention will be implemented in a non-random sequence across the three facility groups.

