#### Clients

All adult clients who have at least one visit to a community health facility for the above types of services within the prior two weeks, and who meet the following inclusion criteria will be eligible to participate in the data collection: over 18 years of age; speak English; mentally and physically capable of completing an interview; not determined by clinician discretion as inappropriate to contact; not involved in another community health care focused survey; and not living in aged care facilities or gaol.

Each week 20 eligible clients who have not previously participated in the study will be randomly selected from the electronic medical records of each of the three groups of facilities (60 clients per week in total). Selected clients will be mailed an information letter then contacted by phone and asked to participate in a telephone interview. As indicated in Figure 1, the three groups will have different numbers of clients participating in the surveys in the baseline and follow-up periods due to the staggered multiple baseline design. The study is anticipated to recruit 750, 1500 and 2250 clients in the baseline period for groups 1, 2 and 3 respectively, and 1875, 1125 and 375 clients in the follow-up period for these groups.

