### Sample size

Assuming a baseline prevalence of 50% for all forms of preventive care delivery (worst case scenario), the study will have 80% power to detect a difference of between 4.7% to 21.8% in the assessment of each health risk between baseline and follow-up for the three groups at the 1% significance level. Power estimates for the provision of brief advice and referral for all four risk behaviours are conservatively based on the expected number of smokers; as smoking is the least prevalent risk behaviour [1]. The sample in the third group of facilities (which has the shortest follow-up period) is expected to include approximately 450 (20%) smokers in the baseline period and 75 smokers during the follow-up period. With a brief advice prevalence of 50% at baseline, the study will have over 80% power to detect a 20.9% improvement in the prevalence of such care (i.e. a change from 50.0% to 70.9%). Similarly, with an estimated prevalence of 50% for offering a referral prior to the intervention, the study will have over 80% power to detect a 20.9% improvement in prevalence of such care (i.e. a change from 50.0% to 70.9%).

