#### Preventive care delivery

##### Client data

For each outcome, evaluation of intervention effectiveness will involve fitting a segmented logistic regression model, including separate intercepts and slopes at baseline, during the intervention and at follow-up (the three "segments") [74,75]. A statistically significant coefficient for the intercept and/or slope during the intervention or follow-up will indicate a change in the outcome measure following the intervention for each group. Standard errors of coefficients, and hence p-values and confidence intervals, will be estimated using bootstrapping [76]. In the first set of models the outcome of interest will assess client reported assessment of risk behaviour. The second set of models will be restricted to those subjects who report a risk behaviour, with separate models assessing whether or not the community health clinician provided brief advice, or offered a referral.

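### The stated 80% power for a 20.9-point gain in brief advice or referral belongs to a simple two-proportion comparison, not to the segmented-model coefficients by which the protocol judges effectiveness

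*Protocol article*

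**What the plan says.** The Sample size section frames detectable differences as changes "between baseline and follow-up for the three groups at the 1% significance level", assuming 50% baseline prevalence. For assessment it gives a range of 4.7% to 21.8%. For brief advice and referral it uses smokers as the smallest at-risk group, and group 3 because its follow-up is shortest: "approximately 450 (20%) smokers in the baseline period and 75 smokers during the follow-up period". On that basis it claims that "the study will have over 80% power to detect a 20.9% improvement in the prevalence of such care" ("i.e. a change from 50.0% to 70.9"%).

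The Client data section plans something else for each outcome: "fitting a segmented logistic regression model, including separate intercepts and slopes at baseline, during the intervention and at follow-up". A significant intercept and/or slope coefficient in the intervention or follow-up segment is taken to show change, for each group. Brief advice and referral are modelled only in clients who report the risk. The article does not connect the power figures to this model.

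**The concern.** A comparison of two period prevalences uses all the data in each period to estimate one average. A segmented model with its own slope in every period estimates a level at the edge of each segment, which is much less precise. It may also project the baseline trend forward, which costs more. A detectable difference computed for the first does not carry over to the second.

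The 80% statement is the article's justification of sample size for advice and referral. If the planned coefficients lack that power, a non-significant result in group 3 smokers could be read as no change in a study believed able to see a 20.9-point gain, when most such gains would be missed.

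**Working it through.** **Inputs.** Baseline: "750, 1500 and 2250 clients in the baseline period for groups 1, 2 and 3 respectively". Follow-up: "1875, 1125 and 375 clients in the follow-up period for these groups". The intervention segment is 12 months ("sequential implementation of a 12 month practice change intervention in three administratively defined groups"). Recruitment is 20 per week × 50 weeks × 75% consent = 750 per group per year, or 62.5 per month. Group 3 therefore has segments of 2250/62.5 = 36, 12 and 375/62.5 = 6 months. At 20% smokers that is 450, 150 and 75 smokers. Alpha is 1%; sidedness is not stated.

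**Step 1: reproduce the stated figure.** Two-proportion test, pooled variance under the null, no continuity correction:
- Pooled p = (450×0.5 + 75×0.709)/525 = 0.530; SE under the null = √[0.530×0.470×(1/450 + 1/75)] = 0.0622.
- SE under the alternative = √[0.25/450 + 0.709×0.291/75] = 0.0575.
- Power = Φ[(0.209 − 2.576×0.0622)/0.0575] = 80.1%. The difference detectable with 80% power is 20.9 points.

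The match is exact. Other variants do not fit: one-sided 1% gives 86.8%, two-sided 5% gives 93.5%, and a continuity correction needs 482 rather than 450 at baseline.

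**Step 2: the planned coefficients, same effect, group 3 smokers.** The change is ln(0.709/0.291) = 0.891 on the log-odds scale. Each client contributes information p(1−p): 0.25 at 50% and 0.2063 at 70.9%. With a free slope, the variance of a level at a segment boundary is about 4/(n×p(1−p)), four times that of the segment average. Effect shape and coding are my assumptions.

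- *Step at intervention start, intervention-level coefficient.* Variance = 4/(450×0.25) + 4/(150×0.2063) = 0.0356 + 0.1293 = 0.165; SE 0.406; z = 2.19; power = Φ(2.19 − 2.576) = 35%.
- *Step at follow-up start, level against the end of the intervention segment.* Variance = 4/(150×0.25) + 4/(75×0.2063) = 0.1067 + 0.2585 = 0.365; SE 0.604; z = 1.47; power 14%.
- *Follow-up level against the baseline trend projected to month 48.* Baseline part = [1 + 12×(30/36)²]/(450×0.25) = 0.0830; adding 0.2585 gives 0.3415; SE 0.584; z = 1.52; power 15%.
- *Linear ramp over the intervention, intervention-slope coefficient.* Slope change 0.891/12 = 0.074 per month; SE 0.050; power 14%.

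Simulation (4000 trials per shape, fitted six-parameter logistic model, two-sided 1%), with analytic values beside it:

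| Effect shape | Carrying coefficient: analytic / simulated | Any of four: analytic / simulated | Two-proportion test, same data |
|---|---|---|---|
| Step at intervention start | 35% / 34% | 37-43% / 35-41% | 80% |
| Step at follow-up start | 14-15% / 12% | 15-17% / 14% | 80% |
| Ramp over intervention | 14-15% / 12-13% | 16-27% / 15-23% | 80% |

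Ranges within a cell reflect two codings: change from the previous segment, or change from the baseline trend. At 5%, the carrying coefficients reach about 31-59%. Any of four reaches 39-72%, but then with a type I error of about 16%.

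**Step 3: the assessment range.** The method of step 1 gives detectable differences of 7.3 points (750 v 1875), 6.7 (1500 v 1125) and 9.5 (2250 v 375). None is 4.7 or 21.8. For the intervention-level coefficient with a step at intervention start, variance = 4/(baseline n × 0.25) + 4/(750×p(1−p)):
- At 4.7 points the log-odds change is 0.189 and the SEs for groups 1, 2 and 3 are 0.207, 0.179 and 0.169. Power is about 5%, 6% and 7%.
- At 21.8 points the change is 0.935 and the SEs are 0.218, 0.192 and 0.183. Power is about 96%, 99% and 99%.

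**Step 4: a contrast the sample nearly supports.** Follow-up against baseline level at segment midpoints, group 3 smokers: variance = 1/(450×0.25) + 1/(75×0.2063) = 0.0089 + 0.0646 = 0.0735; SE 0.271; z = 3.28; power = Φ(3.28 − 2.576) = 76%.

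**The case against.** The best defence has four parts.

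- **The article is not the full plan.** It does not fix time origin, coding, effect shape or how the coefficients combine, and such detail may sit in a document not shown. This stands as a limit on precision: no single power figure follows from the text. A 2-df joint test of intervention level and slope reaches 56% under the most favourable shape, and the midpoint contrast about 76%. The article announces neither; its stated rule is significance of intercept and/or slope coefficients.
- **The smoker case is a deliberate floor.** This stands. The Background gives 86% with inadequate vegetable intake. With that denominator and a 20.9-point step at intervention start, the intervention-level coefficient has about 89%, 96% and 98% power in groups 1 to 3. A reader might infer that every advice and referral outcome falls short; the documents do not support that.
- **Assessment is not uniformly short of power.** This also stands. A reader might infer that any effect of the planned size would be missed more often than found in every group. At 21.8 points that is untrue, as step 3 shows.
- **The 1% level is stated only for sample size.** True, but at 5% the group 3 smoker coefficients still fall short of 80%.

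Nor is the 20.9-point arithmetic wrong. It is correct for a test the client analysis does not plan.

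**Conclusion.** The point holds for the figure it concerns. The 80% power at 20.9 points is that of a baseline versus follow-up comparison of proportions in group 3 smokers. Under the stated decision rule, at 1%, the effect-carrying coefficient has about 14-35% power and any of four about 14-43%. This rests on independent clients (facility clustering ignored), even recruitment, time anchored at segment boundaries, and the three effect shapes tried.

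For assessment the conclusion is narrower: the 4.7% to 21.8% range does not reproduce from the group sizes and is not tied to the model. The two-proportion origin is demonstrated only for 20.9 points. This is a mismatch between sample size and analysis that makes the power statement wrong as written. It does not show that the trial is underpowered throughout.

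**What to change.** Do one of two things:

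1. Recompute the detectable differences by simulating the segmented model that will be fitted. Restate them for assessment, brief advice and referral by group, with the assumed effect shape over time, the coding of intercepts and slopes, and alpha with its sidedness.
2. Name one primary follow-up versus baseline contrast from the fitted model and state its power. Segment midpoints are one example, at about 76% for group 3 smokers on the figures above.

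In either case, stop presenting the two-proportion figure as the power of the segmented coefficients, and correct or explain the 4.7% to 21.8% range. The cost is a short simulation, revised wording and less favourable stated figures. No extra clients are needed.

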### Statistical analysis

#### Sample characteristics

Clients and clinicians completing the surveys will be compared to eligible non-participants in terms of characteristics and clinical descriptors using chi-square analyses. The characteristics of clients and clinicians obtained from their respective surveys at baseline will be compared with equivalent data at follow-up.

#### Preventive care delivery

##### Client data

For each outcome, evaluation of intervention effectiveness will involve fitting a segmented logistic regression model, including separate intercepts and slopes at baseline, during the intervention and at follow-up (the three "segments") [74,75]. A statistically significant coefficient for the intercept and/or slope during the intervention or follow-up will indicate a change in the outcome measure following the intervention for each group. Standard errors of coefficients, and hence p-values and confidence intervals, will be estimated using bootstrapping [76]. In the first set of models the outcome of interest will assess client reported assessment of risk behaviour. The second set of models will be restricted to those subjects who report a risk behaviour, with separate models assessing whether or not the community health clinician provided brief advice, or offered a referral.

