## Methods/Design

### Study aim

The primary aim of the study is to assess the effectiveness of a multi-strategic practice change intervention in increasing clinician provision of recommended preventive care (risk assessment, brief advice, and referral) [21-23,49] for each of four chronic disease health risk behaviours (smoking, inadequate fruit and vegetable consumption, risky alcohol use, and inadequate physical activity) across a network of community health facilities.

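### Any one of four segment coefficients, of either sign, counts as a change in each group, so the rule exceeds its 1% level and does not test for an increase in care

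*Protocol article*

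**What the plan says.** The Study aim is directional: to assess the "effectiveness of a multi-strategic practice change intervention in increasing clinician provision of recommended preventive care", for three care elements and four risk behaviours.

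Under Statistical analysis, Client data, intervention effectiveness is evaluated for each outcome by a segmented logistic regression with its own intercept and slope in the baseline, intervention and follow-up segments. The rule for reading that model is: "A statistically significant coefficient for the intercept and/or slope during the intervention or follow-up will indicate a change in the outcome measure". The sentence goes on to apply it to each group. Standard errors are to come from bootstrapping. The section gives no significance level, no required sign, no joint test and no main contrast.

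The 1% level appears only under Sample size, where power is stated for a simple difference in prevalence "between baseline and follow-up for the three groups at the 1% significance level". For brief advice and referral, the worked case is group 3, with 450 smokers at baseline and 75 at follow-up, and an improvement from 50.0% to 70.9%.

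**The concern.** The article does not leave the decision rule to a later document. It writes the rule out, and the rule has three weaknesses.

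- **Four routes.** A signal in any one of four coefficients is enough, so the chance of a false signal exceeds the level used for each coefficient.
- **No direction.** A fall in care satisfies the rule as well as a rise. If the level drops while the slope rises, or the reverse, nothing says how to turn the pair into a statement that care increased.
- **No link to the powered comparison.** The sample size rests on one baseline versus follow-up difference in prevalence. None of the four coefficients is that difference.

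At stake is the primary conclusion: whether the intervention raised care in each group of facilities.

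**Working it through.** **1. The plan's own figure.** Group 3 smokers: n1 = 450, n2 = 75, p1 = 0.500, p2 = 0.709, two-sided 1% (z = 2.576), pooled variance under the null, no continuity correction.

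- Pooled p = (450 × 0.500 + 75 × 0.709)/525 = 0.530.
- SE under the null = √[0.530 × 0.470 × (1/450 + 1/75)] = 0.0622.
- SE under the alternative = √[0.25/450 + 0.709 × 0.291/75] = 0.0575.
- Power = Φ[(0.209 − 2.576 × 0.0622)/0.0575] = 0.801.

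Solving for 80% power gives 20.9 points, as stated. A one-sided 1% level gives 19.4 and a two-sided 5% level 17.2, so the plan's figure matches one two-sided test at 1%.

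**2. Design inputs.** Twenty clients are selected per group per week (Clients section). With 75% consent (notes to Figure 1) that is 15 interviews a week, in a 50-week year. Dividing the planned numbers by 15 gives the baseline and follow-up lengths; the 12-month intervention is 50 weeks.

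| Group | Baseline | Intervention | Follow-up |
|---|---|---|---|
| 1 | 750/15 = 50 weeks | 50 weeks | 1875/15 = 125 weeks |
| 2 | 1500/15 = 100 weeks | 50 weeks | 1125/15 = 75 weeks |
| 3 | 2250/15 = 150 weeks | 50 weeks | 375/15 = 25 weeks |

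**3. False-signal rate with no change.** If the four coefficients were independent, the rate would be 1 − 0.99⁴ = 3.9%. They are correlated, so their joint normal distribution was taken from the inverse information matrix of the weekly design. Two codings were used: (a) change at each breakpoint; (b) each later segment relative to the extrapolated baseline line. With constant prevalence and equal weekly numbers, the correlations depend on neither the prevalence nor the number per week. The rates therefore also apply, approximately, to the at-risk subsets used for advice and referral.

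| Group | Any of four at 1%, (a) | Only negative, (a) | Any of four at 1%, (b) | Only negative, (b) |
|---|---|---|---|---|
| 1 | 3.5% | 46% of signals | 3.0% | 50% of signals |
| 2 | 3.2% | 42% | 3.7% | 49% |
| 3 | 3.6% | 45% | 3.5% | 44% |

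Separate runs of the same calculation reached up to 3.8%. Fitting the logistic model to 1,500 simulated null trials per group, coding (a), gave 3.4%, 2.5% and 5.0% for groups 1 to 3 (Monte Carlo standard error about 0.5 points). Another set of runs for group 3 gave 3.1 to 3.5%. The checks agree broadly with the table.

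**4. At least one of three groups, one outcome.** Under (a): 1 − (1 − 0.0347)(1 − 0.0319)(1 − 0.0358) = 9.9%. Coding (b) also gives 9.9%.

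**5. A true fall.** With prevalence falling from 50% to 40% in group 1 at the start of the intervention and staying there, the rule was met in 28% of 1,000 simulated trials at 1%. The example is illustrative.

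**6. After the change.** One joint 4-df test per group and outcome at 1% has a 1.0% error rate, or 1 − 0.99³ = 3.0% for at least one of three groups. Bonferroni over four coefficients uses 0.01/4 = 0.0025 each. At 0.0025 two-sided (z = 3.023), the calculation in step 1 needs 23.5 points for 80% power.

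**The case against.** The strongest reply is that the inflation is modest. At the only level the document states, the error per group and outcome stays below 4%, under a conventional 5%. The aim and the power statement both point upward, coefficients carry signs, and a two-sided test read with its sign is normal practice. The sentence speaks of a change and does not say that any change proves effectiveness.

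Much of this is fair, but three points survive. The rate is still three to four times the stated 1% and reaches about 10% across the groups. The rule sits in the paragraph that defines how effectiveness is evaluated. Reading the sign does not help when level and slope disagree.

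Some stronger readings are tempting but not supported:

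- **Raw intercepts.** Taking the separate intercepts literally, each would test whether prevalence is 50%, and the rule would nearly always be met at other prevalences. But the text says a coefficient indicates a change, which implies change coding.
- **Error rates at 5%.** The document never gives that level.
- **Counting every coefficient, group and outcome together.** The expected number of false positives in such a count is simply the nominal rate. The aim treats each behaviour separately, and multiplicity across outcomes is commonly left to the analysis plan.
- **A sustained gain would be missed.** Under breakpoint coding such a gain gives zero follow-up coefficients, but it still appears in the intervention coefficients, which the rule also counts.
- **A single pooled, trend-adjusted contrast is needed.** This is one option with a real price. With 15 interviews a week, 50% prevalence and no clustering, group 1 could detect only 50% to about 92% and would carry about 4% of the pooled weight. The pooled detectable difference for smokers would be about 24.7 points, against the planned 20.9 for group 3 alone.

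**Conclusion.** The point holds as a badly fixed decision rule. At 1%, with change-coded coefficients and no true change, it gives about 3.0 to 3.8% false signals per group and outcome, and about 10% for at least one of three groups. Some 42 to 50% of those signals have only negative coefficients. The rule neither requires an increase nor settles conflicting level and slope terms, and it does not test the baseline to follow-up difference that was powered.

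These figures assume that the 1% level from Sample size governs the analysis, that tests are two-sided, that weekly numbers are as planned, and that the bootstrap standard errors are correct. A different level would change the rates. The missing direction and the missing main test do not depend on any of these assumptions.

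**What to change.** In the Client data section:

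1. State the significance level for the analysis (1%, to match Sample size) and that the coefficients are changes in level and slope.
2. For each group and outcome, replace the any-coefficient rule with one joint 4-df test of the intercept and slope changes at 1%, or test each coefficient at 0.0025.
3. Claim effectiveness only when that test is significant and the model-estimated prevalence of care is higher at follow-up than at baseline.
4. Report the individual coefficients as descriptive.

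This changes wording only and needs no new data. It leaves fewer routes to a positive result and slightly less power. The 23.5 against 20.9 points illustrates the cost of 0.0025 in the plan's two-proportion calculation; it is not the power of the segmented model. The direction condition in item 3 is not adjusted for trend, so where care was already rising at baseline, the descriptive coefficients must be read with it.

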**Methods/Design:**

A multiple baseline study will be conducted involving all 56 community health facilities in a single health district in New South Wales, Australia. The facilities will be allocated to one of three administratively-defined groups. A 12 month practice change intervention will be implemented in all facilities in each group to facilitate clinician risk assessment of eligible clients, and clinician provision of brief advice and referral to those identified as being 'at risk'. The intervention will be implemented in a non-random sequence across the three facility groups. Repeated, cross-sectional measurement of clinician provision of preventive care for four individual risks (smoking, poor nutrition, risky alcohol use, and physical inactivity) will occur continuously for all three facility groups for 54 months via telephone interviews. The interviews will be conducted with randomly selected clients who have visited a community health facility in the last two weeks. Data collection will commence 12 months prior to the implementation of the intervention in the first group, and continue for six months following the completion of the intervention in the last group. As a secondary source of data, telephone interviews will be undertaken prior to and following the intervention with randomly selected samples of clinicians from each facility group to assess the reported provision of preventive care, and the acceptability of the practice change intervention and implementation.

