**Figure 1 F1:**
[figure not shown]
**Overview of multiple baseline study showing three phase rollout, intervention periods and outcome measurement**. ^a ^Not randomly allocated. ^b ^Calculated on 50 weeks of data collection per year. ^c ^Based on a 75% consent rate to client survey.

The multiple baseline study design provides a number of advantages that are relevant to the conduct of complex health service research interventions [51,52]. Firstly, the design provides the opportunity for all facilities to participate in the intervention and all clients to receive the intervention (a key motivational requirement for clinician engagement) [52]. Secondly, its sequential implementation allows for any effect of extraneous variables on the outcomes to be monitored [52]. Finally, the design addresses the practical difficulty of recruiting a sufficient number of similar community health facilities, and is more efficient because each group is used as its own control [51,52].

The study is funded by the Hunter Medical Research Institute, and a partnership grant from the National Health and Medical Research Council (application ID: APP1016650) in partnership with the Hunter New England Local Health District. Ethical approval to conduct the study has been obtained from the Hunter New England Human Research Ethics Committee (approval No. 09/06/17/4.03) and University of Newcastle Human Research Ethics Committee (approval No. H-2010-1116).

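### The planned model judges each group only against its own projected baseline trend, so shared shocks and season can pass as intervention effects, and no network-wide result is defined

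*Protocol article*

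**What the plan says.** The Client data section specifies a segmented logistic model for each outcome, "including separate intercepts and slopes at baseline, during the intervention and at follow-up". Its decision rule is that a statistically significant intercept and/or slope in the intervention or follow-up segment "will indicate a change in the outcome measure following the intervention for each group". Standard errors come from bootstrapping. The section names no calendar-time term, no contrast with groups still at baseline and no pooled effect.

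Three other places bear on this:
- Study design and setting gives as an advantage of the design that "its sequential implementation allows for any effect of extraneous variables on the outcomes to be monitored". It also says that the design "is more efficient because each group is used as its own control".
- The same section states: "The intervention will be implemented in a non-random sequence across the three facility groups".
- The Study aim asks about effectiveness "across a network of community health facilities".

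The Contamination section does look at change before implementation in each group, but only to gauge contamination.

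**The concern.** All 56 facilities receive the intervention, in a sequence that is not random, and there is no external control. The groups still waiting are the only concurrent untreated comparison. The design section uses them to justify staggering, yet the decision rule never does. If something district-wide shifts client-reported care, such as a policy, a campaign or a recording change, it is credited to whichever group happens to be starting.

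Season is exposed in the same way. The three baselines last 12, 24 and 36 months, all whole years. The follow-ups last 30, 18 and 6 months, so each contains the same extra half-year, and group 3's follow-up is only that half-year.

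The rule also returns three verdicts per outcome. It does not say what the trial concludes about the network if they differ.

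**Working it through.** **Timeline.** The Clients section and the notes to Figure 1 give 20 selected clients per group per week, 75% consent and 50 weeks: 20 × 0.75 × 50 = 750 per group per year, or 62.5 per month. Dividing the stated client numbers by 62.5:
- baseline: 750, 1500, 2250 → 12, 24, 36 months
- follow-up: 1875, 1125, 375 → 30, 18, 6 months

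With a 12-month intervention each group totals 54 months, as stated: measurement "will occur continuously for all three facility groups for 54 months via telephone interviews". Untreated groups are 2 and 3 in months 12–24 and group 3 in months 24–36. There are none after month 36.

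**The plan's own figure.** Sample size gives over 80% power for 50.0% to 70.9% with 450 and 75 smokers in group 3. Taking the 1% level as two-sided:
- pooled proportion (225 + 53.175)/525 = 0.530
- null SE √[0.530 × 0.470 × (1/450 + 1/75)] = 0.0622
- alternative SE √[0.25/450 + 0.709 × 0.291/75] = 0.0575
- (0.209 − 2.576 × 0.0622)/0.0575 = 0.85, so power is 0.80

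It reproduces. It is a before-and-after comparison within one group, and uses neither the segmented model nor the other groups.

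**Shared calendar change, no intervention effect.** 500 simulated trials per scenario; 62 clients per group-month; prevalence 50% at the start; each coefficient tested at two-sided 1%. The own-trend rule flags a group if any of its four intervention or follow-up coefficients is significant. The joint model here has group effects, shared month effects and one level term each for intervention and follow-up. The size of the shock is an assumption, so a range is shown.

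| Shared calendar change | Own-trend: group 2 | Own-trend: any group | Joint: either term |
|---|---|---|---|
| none | 3.8% | 11% | 1.8% |
| 5-point step, month 24 | 11% | 16% | 1.4% |
| 10-point step, month 24 | 46% | 54% | 1.8% |
| linear, 15 points over 54 months | 3.4% | 11% | 2.6% |

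Month 24 is when group 2 starts. A step from 50% to 60% is ln(0.6/0.4) = 0.405 in log-odds. The mean follow-up level coefficients under that step were 0.40, 0.42 and −0.19 for groups 1, 2 and 3. In groups 1 and 2 the shock appears as benefit. In group 3 it tilts the baseline slope and appears as harm.

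**Precision.** Standard errors come from the information matrix of the logistic model at p = 0.5, with independent clients. Detectable points from 50% = 100 × [1/(1 + exp(−3.417 × SE)) − 0.5], where 3.417 = 2.576 + 0.842. Results use unrounded SEs.

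| Contrast | SE (log-odds) | Points |
|---|---|---|
| Own trend, start of follow-up, group 1 | 0.399 | 29.6 |
| the same, group 2 | 0.221 | 18.1 |
| the same, group 3 | 0.245 | 19.8 |
| Joint, shared months, common levels and slopes: mid-intervention | 0.087 | 7.4 |
| the same: start of follow-up | 0.118 | 10.0 |
| Pooled own trends, common slopes, no calendar term: mid-intervention | 0.089 | 7.5 |
| the same: start of follow-up | 0.116 | 9.8 |
| Joint, plus group-specific trends: mid-intervention | 0.152 | 12.7 |
| the same: start of follow-up | 0.211 | 17.3 |

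On a linear probability scale (3.417 × SE/4) the joint start-of-follow-up figure is 10.1, and the last two rows are 13.0 and 18.1.

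**Shape of the effect.** Take a noise-free 20-point effect that declines linearly to zero over 30 months of follow-up. A joint model with constant levels only returns 24.2 for intervention and 21.7 for follow-up, against true averages of 20 and 12.2, because decay in treated groups is read as calendar change. With common slopes added, it recovers the truth exactly.

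**The case against.** Replication across staggered groups is the ordinary logic of a multiple baseline design, and a reader can compare the three results by eye. The text does not exclude one model holding all groups, and an analysis plan that is not shown may add seasonal terms or covariates. Their absence is not a finding. What stands is that the article does fix a decision rule, and that rule contains no contrast between groups and no network result.

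A reader might infer more than the documents support:
- *That the waiting groups are the only protection against secular change.* They are not. Each group has its own baseline slope, and a shared linear trend of 15 points left the any-group rate at 11%, the same as with no trend.
- *That ignoring the waiting groups is what costs precision.* It is not. Pooling with own trends and no calendar term already gives 7.5 and 9.8 points, and adding calendar months to that model worsens it to 12.7 and 17.3. The gain over the group models comes from pooling. The concurrent groups protect against bias.
- *That group 1 could detect only about 60 points.* That comes from a linear-scale contrast at mid follow-up and is impossible from 50%. The logistic figure is 41.7, and the protocol tests segment coefficients, not that contrast.

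The remedy also has limits: concurrent control ends at month 36, and a pooled model without slopes would mislead if the effect fades. Fading is plausible, since Comparison sites says that some strategies run only during the intervention period.

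**Conclusion.** The point holds in a limited form and should be acted on. The analysis as written leaves shocks, season and non-linear calendar change on the intervention and follow-up terms, does not use the feature that the design section offers against them, and defines no answer to the network question.

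The size of the bias depends on the shock. At month 24, a 5-point step raises group 2's false-positive rate from 3.8% to 11%, and a 10-point step raises it to 46%. With linear secular change there is no added error. At the start of follow-up the group models detect 29.6, 18.1 and 19.8 points, against about 10 for the joint model with common slopes.

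All figures assume independent clients, 50% prevalence and a two-sided 1% level. Clustering within facilities would widen every detectable difference. The 1.8% rate is for the joint model with level terms only. Adding common slopes keeps the protection, because shared month effects still absorb a shared step, but reading four terms singly would again exceed a nominal 1%.

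**What to change.** Add to the Client data section, as the analysis that answers the network question, one logistic regression over all three groups with:
- group effects
- shared calendar-time effects (months, or a trend plus an annual harmonic)
- common level and slope terms for the intervention and follow-up periods, so that decay is not read as calendar change

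Name in advance the contrast or joint test that gives the network result. Keep the group-specific segmented models alongside, test group-by-period interaction, and report a sensitivity analysis restricted to months 0–36. State that no untreated group exists after month 36, so that group 2's follow-up and all of group 3's intervention and follow-up rest on the shared-calendar assumption and on groups already treated.

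**Cost.** Analysis wording only; the data are already planned. The joint model assumes a common calendar effect and a common effect shape across groups. The calendar assumption is partly checkable in months 0–12 (all groups) and 12–24 (groups 2 and 3). If group-specific trends prove necessary, detectable differences rise to about 13 points at mid-intervention and 17 to 18 at the start of follow-up. Contamination of waiting groups, which the protocol considers unlikely, would pull the joint estimate towards no effect.
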